## Abstract

**Background and Rationale::**

Uncertainty persists over the optimal management of blood pressure (BP) in the early phase of acute ischemic stroke (AIS). This study aims to determine the safety and effects of intensive BP lowering on cerebral blood flow (CBF) and functional in AIS patients treated with intravenous thrombolysis.

**Methods::**

In a randomized controlled trial, 54 thrombolysed AIS patients with a systolic BP of 160 to 180 mm Hg will be randomized to early intensive BP lowering (systolic target range 140–160 mm Hg) or guideline-based BP management (systolic range 160–180 mm Hg) during first 72-hours using primarily intravenous labetalol. We hypothesize that early intensive BP lowering will not reduce CBF by 20% and/or increase the volume of hypoperfused tissue by >20% on computed tomographic perfusion. Clinical outcome will be assessed using a dichotomized modified Rankin scale (scores 0–1 as excellent outcome vs scores 2–6 as dead or dependent) at 90 days. Other outcome would be symptomatic intracerebral hemorrhage. The trial is registered at ClinicalTrials.gov, NCT03443596.

**Conclusion::**

This randomized study will provide important information about the physiological effects of BP reduction on cerebral perfusion after intravenous thrombolysis in AIS.

## Introduction and rationale

1

Elevated systolic blood pressure (BP), defined as >140 mm Hg, is commonly observed in patients with acute ischemic stroke (AIS).^[1]^ Potential mechanisms and associations include pre-existing hypertension,^[1]^ activation of neuroendocrine systems,^[2]^ stress of hospitalization,^[3]^ location of the infarct,^[4]^ stroke subtype,^[5]^ severity,^[6]^ and a homeostatic response to raised intracranial pressure.^[7]^ Whether treatment of this acute hypertensive response improves clinical outcome is unknown.^[7,8]^ Arguments in favor of treatment include the strong positive relationship between degree of elevation in BP and death or dependency,^[9]^ cerebral edema,^[10]^ early and late stroke recurrence,^[11,12]^ and extrapolation of potential benefits in acute intracerebral hemorrhage (ICH).^[13–15]^ Arguments against treatment center on the natural tendency for BP to normalize within a few days of presentation,^[1,5,6]^ and potential harms associated with altered cerebral perfusion related to dysfunction of autoregulation.^[7,16,17]^ Some studies suggest that adverse outcomes are associate with early antihypertensive therapy.^[18,19]^

The primary aim of the study is to determine the effect of early intensive BP lowering (systolic BP target 140–160 mm Hg) initiated within 6 hours of symptom onset and maintained for 72 hours in AIS patients treated with intravenous tissue plasminogen activator (IV-tPA) on cerebral blood flow (CBF), measured with computed tomographic (CT) perfusion imaging. We hypothesize that this treatment approach is safe and that such magnitude of BP lowering does not reduce CBF by 20% and/or increase the volume of hypoperfused tissue by >20% on CT perfusion or adversely affect functional outcomes at 90 days. Secondary aims are to obtain preliminary estimates of the clinical impact of early intensive BP lowering on functional outcomes and symptomatic intracerebral hemorrhage (sICH).

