### Statistical analysis

2.12

Data will be analyzed blind to treatment group according to the intention-to-treat principle by an independent biostatistician. Continuous variables will be presented as mean (SD) and nominal variables tabulated as absolute and/or relative frequencies. Comparisons between binary outcomes will be performed using Fisher exact test. Continuous variables will be compared using the unpaired *t* test and Mann-Whitney *U* test as indicated. Comparisons of BP and NIHSS scores between the 2 groups at different time-points will be analyzed using repeated-measures analysis of variance for the overall effect. Finally, the relative changes in BP, CBF, and NIHSS scores at 1, 24, and 72 hours after the initiation of treatment, and 90-day outcomes, will be compared using analysis of covariance. Baseline BP and use of antihypertensive medications before admission will be used as covariates in analyses of BP differences. Baseline NIHSS will be used as a covariate in analyses of stroke severity. Statistical significance is set at the 5% level. There would be no interim analysis (Table 3).

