## Discussion

3

As a U-shaped relationship of systolic BP and outcomes after IV-tPA is suggested in various studies,^[8,10,12]^ both high and low systolic BP are considered harmful. Interestingly, the nadir for optimal outcome appears to be a systolic BP of 140 to 160 mm Hg. Thus, we hypothesize this systolic BP as being the best target for functional outcome and reduced risk of sICH.

Labetalol was chosen for BP lowering because of ready availability, minimal adverse effects on heart rate, and cardiac output due to being a mixed α and β antagonist effects, rapid onset of action (5 minutes) and reasonable duration of action (3–6 hours). Studies indicate stable effects of labetalol on CBF, cerebral oxygen consumption, and cerebral circulation.^[21,22]^ There is good experience of the use of labetalol in patients with AIS^[23]^ and it has a predictable and uniform dose-response relationship.^[23]^

With serial BP measurements (including comparison of different intensities of BP lowering), NIHSS and repeated CT perfusions, this study will provide mechanistic data to elucidate the relationship between BP, cerebral perfusion, and functional outcomes in thrombolysed AIS cases. Our findings may assist the ongoing studies (such as ENCHANTED BP intensity arm results due in early 2019) and improve the design of future clinical trials of BP management in AIS (in thrombolysed and endovascularly treated) patients.

Finally, we wish to clarify that study is not aimed at evaluating the relationship between early intensive BP reduction and arterial recanalization or persisting occlusion. Study participants are recruited after the arterial recanalization treatment strategies (IV thrombolysis and/or EVT) have already been implemented. While the first CT perfusion serves as the baseline for a particular patient, subsequent perfusion scans provide information about the longitudinal changes in cerebral hemodynamic parameters in response to the changes in BP levels.

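### The hypothesis covers clinical safety and 90-day function, which 27 to 30 patients per arm and tests of difference cannot support

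*Protocol article*

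**What the plan says.** In the protocol article, Introduction and rationale (section 1), the hypothesis reads "We hypothesize that this treatment approach is safe and that such magnitude of BP lowering does not reduce CBF by 20" per cent. It goes on to hypoperfused volume and ends "or adversely affect functional outcomes at 90 days". No margin defines an adverse effect on function. The next sentence is more modest: "Secondary aims are to obtain preliminary estimates of the clinical impact of early intensive BP lowering on functional outcomes", and it adds symptomatic intracerebral haemorrhage (sICH).

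Other places bear on how the clinical part should be read:

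- The Abstract's background paragraph gives determining safety as an aim. Its methods paragraph states the hypothesis for perfusion only, and its conclusion says the study "will provide important information about the physiological effects of BP reduction on cerebral perfusion".
- Outcomes (2.7) makes perfusion primary. Dependency at day 90 (mRS 2 to 6) and sICH are secondary.
- Sample size calculations (2.11) uses CBF and/or hypoperfused volume only. It gives 27 per group, raised to 30. The Abstract gives a total of 54.
- Statistical analysis (2.12) says "Comparisons between binary outcomes will be performed using Fisher exact test", at the 5% level. It also names analysis of covariance for 90-day outcomes.
- The Discussion (section 3) says of the 140–160 mm Hg range that "we hypothesize this systolic BP as being the best target for functional outcome and reduced risk of sICH".

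**The concern.** A hypothesis of safety and of no adverse effect is a claim that harm is absent, or at least smaller than some tolerable amount. Supporting it takes a stated margin, or an interval narrow enough to exclude harm that matters. The article gives no margin, and the clinical comparisons it names are tests of difference. In a trial of this size such tests will usually be non-significant whether or not there is moderate harm.

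The stakes are in the reporting. A null clinical comparison would appear to confirm the hypothesis as written, while the data remain compatible with a large excess of dependency or haemorrhage. The Introduction itself cites possible harm from altered perfusion and studies linking early antihypertensive therapy to adverse outcomes, so harm is the open question.

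**Working it through.** **Inputs from the article.** 27 per group before and 30 after the allowance for losses (2.11); 1:1 allocation (2.3); two-sided 5% level (2.11, 2.12). **Assumptions.** The article gives no rates for dependency or sICH and no clinical margin. I take dependency at 30 to 60%, equal in both arms for the interval calculation. Other assumed values are labelled below.

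**1. The plan's own figure.** The only sizing is for perfusion: difference 20%, SD 15%, 90% power, two-sided 5%. Direct use of these inputs gives n = 2(1.960 + 1.282)² × (15/20)² = 11.8, so 12 per group (13 with the t distribution), not 27. If the SD is widened to 15√2 = 21.2, one possible reading of the remark about within- and between-subject variation, n is 24 (25 with t). I could not reproduce 27 exactly. That is a separate matter; what counts here is that no clinical outcome enters the calculation.

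**2. Dependency when the observed difference is zero.** The half-width of the 95% interval for the risk difference is 1.96 × √(2p(1−p)/n).

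| p (assumed) | n = 27 | n = 30 |
|---|---|---|
| 0.30 | 24.4 points | 23.2 points |
| 0.40 or 0.60 | 26.1 points | 24.8 points |
| 0.50 | 26.7 points | 25.3 points |

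Identical observed rates thus leave about 23 to 27 points of excess dependency inside the interval.

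**3. Chance that Fisher's test detects real harm** (exact power, two-sided 5%, assumed control rate 40 or 50%).

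| True excess | n = 27 | n = 30 |
|---|---|---|
| 10 points | 6.2% | 7.7% |
| 20 points | 20.3 to 22.7% | 25.7 to 25.9% |
| 30 points | 48.1 to 55.0% | 56.1 to 59.6% |

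A true 20-point excess would therefore be missed about 74 to 80% of the time. By the normal approximation, with control rates of 30 to 60%, 80% power needs a true excess of 32 to 37 points at 27 per group, or 31 to 36 at 30.

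**4. sICH.** With no events, the upper limit of the two-sided exact 95% interval is 1 − 0.025^(1/n): 12.8% for n = 27 and 11.6% for n = 30. One event in 27 gives 19.0%. If the true risk were 6% (assumed), the chance of seeing none is 0.94^27 = 18.8% or 0.94^30 = 15.6%. Between arms, Fisher's test needs at least 6 events against 0 for significance.

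**5. Scale.** Showing non-inferiority for dependency at an assumed 10-point margin (one-sided 2.5%, 80% power, equal rates of 30 to 60%) needs (1.960 + 0.842)² × 2p(1−p)/0.10², or 330 to 393 per group. At 15 points it needs 147 to 175. This shows the distance from the present design; it does not propose enlarging the trial.

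**The case against.** The strongest reply is that the article already limits its clinical claim. The sentence after the hypothesis speaks of preliminary estimates, the Abstract states a perfusion-only hypothesis and a physiological conclusion, both clinical outcomes are secondary, and the Discussion calls the data mechanistic and useful for designing later trials. That is correct. It shows what the sponsor probably intends, and it keeps the point small. It does not remove the clinical clauses from the hypothesis.

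A reader might go further and infer three incompatible clinical objectives: no harm, estimation and superiority. The documents do not support this. Expecting no harm is compatible with aiming only for preliminary estimates. The Discussion sentence gives the reason for the chosen range; no superiority objective or test is attached to it.

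A reader might also infer that the sponsor plans to declare safety from a null Fisher test. No passage says so and there is no such decision rule. The risk lies in how the hypothesis could later be read.

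Two further replies hold in part. Fisher's test is valid in small samples and need not be dropped. Details of interval reporting may sit in an analysis plan that is not shown, so their absence from the article is not the fault; the stated hypothesis is.

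**Conclusion.** The point holds as a minor one. The clinical part of the Introduction's hypothesis, and the safety aim in the Abstract, claim more than the design can support. With 27 to 30 per arm and no observed difference, about 23 to 27 points of excess dependency stay possible. Zero sICH in the intensive arm leaves an upper limit of 11.6 to 12.8%. A true 20-point harm would be detected about 20 to 26% of the time.

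The dependency figures rest on assumed rates (30 to 60% for the intervals, 40 or 50% in controls for Fisher power). The conclusion does not change across those ranges, nor between 54 and 60 patients. The sICH upper limits need only the number of patients. Very large harm, above roughly 30 points, would usually be detected, so the trial is not uninformative about function. No endpoint, sample size or primary analysis is affected.

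**What to change.** - Introduction: confine the hypothesis to CBF and hypoperfused volume, dropping the safety wording and the clause on 90-day function. Keep the sentence on preliminary estimates.
- Abstract: align the stated aim with this.
- Discussion: present the sentence on the best target as the rationale for the range, not as a hypothesis this trial tests.
- Outcomes (2.7) and Statistical analysis (2.12), or the full analysis plan: report 90-day mRS and sICH as risk differences with 95% confidence intervals. Fisher's test may stay as a descriptive supplement. State that no conclusion of clinical safety or benefit will be drawn from a non-significant comparison.

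The cost is a few sentences and a more modest stated claim. No patients or procedures are added and clinical management is untouched. The change does not settle how a no-reduction hypothesis for perfusion fits a sample size based on detecting a difference; that is a separate question.

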### Outcomes

2.7

The primary outcome is the assessment of CT perfusion studies and evaluate whether CBF in the affected region reduces by >20% and/or the volume of hypoperfused tissue increases by >20% if BP is treated intensively during the first 72 hours in thrombolysed AIS patents. Secondary endpoint is dependency at day-90, defined by scores 2 to 6 on the mRS. Secondary outcome would be sICH, defined by the Safe Implementation of Thrombolysis in Stroke-Monitoring Study (SITS-MOST) criteria as large local or remote parenchymal ICH (type 2) combined with a neurological deterioration (≥4 points on the NIHSS) from baseline or death within 36 hours.^[20]^ Data are entered prospectively on to case report forms without any personal identifiers.

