### Sample size calculations

2.11

Allowing for within-subject and between-subjects variation, a sample size of 27 patients per group was estimated to allow detection of a difference of 20% [15% standard deviation (SD)] in relative change in CBF and/or the volume of hypoperfused tissue between the early intensive BP lowering and control groups, with 90% power and significance set at 5% (α = 0.050, 2-tailed). The sample size was increased to 30 patients per group to allow for treatment dropouts, crossovers, and potential loss to follow-up.

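### The primary hypothesis is no harm beyond 20%, but the sizing and analysis provide only difference tests at 5%, and 'and/or' leaves open which measure decides

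*Protocol article*

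**What the plan says.** **Hypothesis.** The Introduction and rationale opens the hypothesis with "We hypothesize that this treatment approach is safe" and goes on to say that "such magnitude of BP lowering does not reduce CBF by 20% and/or increase the volume of hypoperfused tissue by >20% on CT perfusion". The Methods paragraph of the Abstract repeats the 20% limits.

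**Primary outcome.** Section 2.7 (Outcomes) uses the CT perfusion studies to "evaluate whether CBF in the affected region reduces by >20% and/or the volume of hypoperfused tissue increases by >20% if BP is treated intensively".

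**Sizing.** Section 2.11 (Sample size calculations) arrives at 27 per group "to allow detection of a difference of 20% [15% standard deviation (SD)] in relative change in CBF and/or the volume of hypoperfused tissue" between the arms, with 90% power and a two-tailed alpha of 0.05. The figure is then raised to 30 per group.

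**Analysis.** Section 2.12 (Statistical analysis) lists Fisher's exact test for binary outcomes, the unpaired t test or Mann-Whitney test for continuous variables, and analysis of covariance for relative changes, CBF among them. It closes with "Statistical significance is set at the 5% level". It gives no margin and no rule for reading a confidence interval against 20%. It does not say whether one or both perfusion measures decide, and it does not name hypoperfused volume.

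**The concern.** The claim to be established is that harm stays below a limit. A difference test asks whether the arms differ at all, which is a different question, and its result can mislead in both directions:

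- A p value above 0.05 may reflect noisy perfusion data as easily as absence of harm. The noisier the data, the likelier that result becomes.
- A p value below 0.05 may come with an interval lying wholly short of 20 points, which agrees with the hypothesis.

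The *and/or* adds a second gap. Read one way, worsening on either measure defeats the hypothesis. Read the other way, a good result on one measure could be offered as support. The text does not choose. At stake is whether the primary result can be tied to the hypothesis by a rule fixed in advance.

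**Working it through.** **Inputs.** From section 2.11: difference 20 points, SD 15%, two-sided alpha 0.05, power 90%, 27 per group. Assumed here: SD 30% as a noisier case, and independence of the two measures where joint power is given.

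**1. The plan's own figure.** Per group, n = 2·SD²·(1.960 + 1.282)²/difference² = 2·15²·(3.242)²/20² = 11.8, so 12. The exact t-test calculation gives 13. The stated 27 does not follow from the stated inputs. The section mentions "Allowing for within-subject and between-subjects variation" but gives no variance components. Solving the t-test power equation for 27 per group and 90% power gives an SD of about 22.2%. The results below are therefore shown at 15% (stated), 22.2% (implied by 27) and 30% (assumed).

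**2. Chance that a true 20-point harm on one measure is non-significant.** SE = SD·√(2/27); noncentrality = 20/SE; 52 degrees of freedom; critical value 2.007.

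| SD | SE | 20/SE | P(non-significant) |
|---|---|---|---|
| 15% | 4.08 | 4.90 | 0.2% |
| 22.2% | 6.04 | 3.31 | 9.9% |
| 30% | 8.16 | 2.45 | 32.8% |

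If the 95% confidence limit is compared with 20 instead, the chance of wrongly excluding a true 20-point harm is 2.5% at every SD.

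**3. The opposite direction.** At SD 15% the 95% half-width is 2.007 × 4.08 = 8.2 points. An observed 9-point reduction has the interval 9 ± 8.2, that is 0.8 to 17.2. It is significant, yet it excludes 20.

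**4. Does a margin rule need more patients for one measure?** With margin 20, one-sided 2.5% and true difference 0, the test statistic has the noncentrality of step 2. Power with 27 per group is 99.8% (SD 15%), 90.1% (SD 22.2%) and 67.2% (SD 30%). These match the power to detect a 20-point difference, so the per-measure sample size is unchanged.

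**5. Requiring both measures.** Under independence, joint power is the square of the single-measure power.

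| SD | True difference 0 | True worsening of 5 points on both |
|---|---|---|
| 15% | 0.998² = 99.6% | 0.950² = 90% |
| 22.2% | 0.901² = 81% | 0.683² = 47% |
| 30% | 0.672² = 45% | 0.438² = 19% |

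For 90% joint power at true difference 0, each measure needs power √0.9 = 0.949. At SD 22.25%, the normal approximation gives n = 2·22.25²·(1.960 + 1.632)²/20² = 31.9, so 32 per group, against the 30 planned.

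**The case against.** **The article never says that p above 0.05 means safe.** This stands. A reader might infer such a rule because only difference tests are listed, but no sentence states it. The supportable point is narrower: the listed tests do not address the stated hypothesis.

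**At the only SD in the document, a 20-point harm is almost never missed.** This also stands: 0.2% at SD 15%. The larger rates need a larger SD. The 22.2% is back-solved from a sample size that does not reproduce, and the 30% is assumed. All these rates are for a single test; they would be lower if several correlated tests all had to be non-significant.

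**A small significant reduction is not harm under section 2.7, which sets the limit above 20%.** Agreed, and this is why the significance test cannot settle the question that section 2.7 poses.

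**Section 2.7 might mean a per-patient threshold, compared by Fisher's test.** Possible, but section 2.11 sizes a continuous relative change with an SD. Fisher's test would again be a test of difference, with no bound.

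**Multiplicity.** A reader might count two measures at two scans and infer an 18.5% chance of falsely declaring harm (1 − 0.95⁴). That counts significant improvements as well. In the harm direction it is 1 − 0.975⁴ = 9.6% if the tests are independent. The article does not fix four tests in any case: section 2.12 lists relative CBF change at 1, 24 and 72 hours and does not name hypoperfused volume. No error rate can be attributed to the plan.

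**A full protocol or analysis plan may hold the missing rule.** Multiplicity details may well be there. The hypothesis, sizing, sidedness of the sizing and tests are all stated in the article, however, and they do not fit one another.

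**Conclusion.** The mismatch holds on the text: a hypothesis bounded at 20%, only difference tests to assess it, and an *and/or* that leaves the deciding measure open. The practical size depends on the SD. The chance that a true 20-point harm on one measure is non-significant is negligible at the stated 15%, about 10% at the SD that 27 per group implies, and about a third at an assumed 30%. The wrong question and the undefined *and/or* remain at any SD.

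Two stronger readings are not supported. A reader might infer that the mismatch makes the trial too small, but the per-measure sample size is the same at true difference 0. A reader might also infer that the trial cannot support its conclusion, but the Abstract's conclusion promises only information on physiological effects. The figures assume normal data, equal SDs in the arms, 27 analysed per group and, for joint power, independent measures with the same SD. Positive correlation would raise joint power towards the single-measure value.

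**What to change.** Change the Abstract, Introduction and sections 2.7, 2.11 and 2.12 so that they state one rule:

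- The estimand is the between-group difference in relative change from baseline, for CBF and for hypoperfused volume. The protocol's own 20 points are the margin.
- No harm is concluded only if the two-sided 95% confidence interval excludes a 20-point worsening for both measures at one scan named in advance, for example 72 hours, with 24 hours supportive.
- The *and/or* is replaced accordingly, and hypoperfused volume is named in section 2.12.
- A p value above 0.05 is stated not to be evidence of safety.

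Requiring both measures needs no split of alpha.

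**Cost.** The change goes beyond wording, because the joint rule lowers power: at 27 per group, to about 81% at SD 22.2% and 45% at SD 30%, and further if there is a small true reduction. The 90% in section 2.11 should be restated for the joint rule, with the SD that actually produced 27.

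**Analysis set.** Keep intention-to-treat as primary. Crossovers can dilute a difference, so an on-treatment analysis may be shown, but only as a sensitivity analysis with a warning. Section 2.8 lets intensive treatment be stopped when it is judged the sole or leading cause of deterioration; excluding those patients would bias the result towards no harm.
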